### 2.4. Sample size

To calculate power, we used a Monte Carlo simulation. We based the simulation on the beta-regression [67]. We assumed the proportion of PIMs were distributed across different time points, as highlighted in Table 1, similar to results reported by McCarthy et al. [68]. The Do-File from STATA/BE used for the calculation is found in S2 File.

**Table 1 pone.0314023.t001:** *Data used for the power calculation*.

Time point	At hospital discharge	Six months after hospital discharge
Proportion of PIMs in intervention group	15%	13%
Proportion of PIMs in control group	10%	12%

Data from McCarthy et al. [68] used to calculate the sample size. Abbreviation: PIMs = Potentially Inappropriate Medication

The variance was set at 0.5, and we assumed the risk of dropout after 6 months was associated with age (see formula below)

P(dropout)=exp(1.1*age-70)/(1.1*age-70+1)
(1)

We calculated the p-value using the likelihood ratio test because we have multiple time points. Under the assumption that age will be related to the dropout rate, we needed 70 patients in each group to achieve a power of 93% at an alpha level of 0.05.

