#### 2.2.4. Medication review

The medication reviews are conducted to optimize the patients’ medication treatment. The process of optimization is through the identification of any PIMs that may be discontinued and to identify if the patients experience any drug-related problems that need to be considered. Hence, the medication review is expected to increase the quality of the patients’ medication treatment.

The definition of prescribing quality indicator used is by Lawrence and Olesen [53]: “*a measurable element of prescribing performance for which there is evidence or consensus that it can be used to assess quality*, *and hence in changing the quality of care provided* [53]”. Inspired by Wallerstedt et al [34] the measureable element of prescribing performance used to assess the quality of the patients’ medication treatment is the number of PIMs. The patients’ medications are registered according to the Anatomical Therapeutic Chemical (ATC) Classification System at level 5 [54]. The medication list is assessed for PIMs by applying: two national screening tools *(Discontinuation List 2024/2025* [35] and *the Seven High-risk Situation Medications* [36], and two international screening tools (STOPP [55] and MERIS [31,37].

The medication reviews are conducted as published by Graabæk et al. [56] but with an addition of a sixth, seventh and eight step to the existing five steps.

The patients are presented with the changes made to the medication treatment in the sixth step. The patients are encouraged to write down any important information in *My Medication Plan*. The suggested medication amendments are not implemented prior to hospital discharge, because these changes may require that the patient has been stabilized. Step 7 includes specific instructions about medication amendments in the electronic discharge summary forwarded to the GP.

As the eight step is a follow-up phone call to the patient approximately seven days after discharge. The follow-up conversations is based on the medication review carried out during hospitalization.

The concepts of motivational interviewing are applied during the medication review to focus on the patients’ needs and wishes [50,51,57,58].

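### Table 1 powers the trial on a scenario with more PIMs in the intervention arm and its main gap at discharge, so the stated 93% is not shown to be power for fewer PIMs after discharge

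*Protocol article*

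**What the plan says.** Section 2.4 describes a Monte Carlo simulation based on beta regression, with proportions taken from a cited study. The rows of Table 1, at discharge and at six months, read "Proportion of PIMs in intervention group 15% 13" (per cent) and "Proportion of PIMs in control group 10% 12" (per cent). The section adds that "The variance was set at 0.5", that dropout by six months depends on age, and that the p-value came from a likelihood ratio test because there are several time points. It concludes that "we needed 70 patients in each group to achieve a power of 93% at an alpha level of 0.05". The do-file is in a supplement (S2 File) that is not shown.

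Three other places bear on this:

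- Section 2.3.2 makes the primary outcome the proportion of PIMs after discharge. The abstract and section 3.1 hope for a reduction.
- Section 2.2.4 says: "The suggested medication amendments are not implemented prior to hospital discharge, because these changes may require that the patient has been stabilized". The amendments go to the GP in the discharge summary.
- Section 2.6.1 plans a beta regression with a group-by-time interaction, a global test across baseline, discharge and six months, and then z-tests at each time point adjusted for multiplicity. Section 2.6 makes p-values two-sided.

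**The concern.** Two features of Table 1 do not fit the trial.

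**Direction.** The intervention is meant to lower the proportion of PIMs, yet the assumed proportion is higher in the intervention arm at both time points.

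**Timing.** The larger gap, 5 points, is at discharge. Section 2.2.4 puts the suggested amendments after discharge, so randomised arms would be expected to be about equal there. At six months, when the amendments have had time to act, the assumed gap is 1 point and favours control.

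A joint test over time points rejects for a gap at any of them. Power calculated from Table 1 with such a test would mostly be power to detect a difference that the intervention, as section 2.2.4 describes it, should not yet have produced. The 93% is the only justification given for 140 patients. A null result could then be read as well-powered evidence of no effect when power for the assumed six-month difference was low.

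**Working it through.** **Inputs from the article.** 70 per arm; alpha 0.05, two-sided; gaps (intervention minus control) of +5 points at discharge and +1 point at six months. On the logit scale these are ln(0.15/0.85) − ln(0.10/0.90) = 0.463 and ln(0.13/0.87) − ln(0.12/0.88) = 0.091.

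**Assumptions made here.** Common variance; time points independent unless a correlation r is given; joint test on 2 df (3 df if baseline enters with zero gap). Six-month numbers per arm were varied over 70, 50, 35 and 19, because the age distribution that drives dropout is not given.

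**Step 1. Can the 93% be reproduced?** Not strictly.

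- A proportion with mean 0.15 has variance at most 0.15 × 0.85 = 0.1275, so 0.5 cannot be a raw-scale variance. Used anyway, it gives about 6% joint power.
- Read as a logit-scale variance, 0.5 gives joint power of 94.6–95.2% (2 df) or 92.0–92.7% (3 df) over the six-month numbers tried.
- A raw SD of 0.080 gives 93.2% (2 df).
- Simulated beta regression reaches about 93% at precision 13. At a mean of 0.125 the SD is then √(0.125 × 0.875/14) = 0.088.

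The stated figure is therefore attainable, but the article does not say under which of these settings.

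**Step 2. Where does the power come from under a joint test?** Each gap d contributes n·d²/(2σ²) to the noncentrality. With 70 per arm throughout:

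| Reading | Discharge term | Six-month term | Discharge share |
|---|---|---|---|
| Raw, SD 0.08 | 70 × 0.05²/0.0128 = 13.67 | 70 × 0.01²/0.0128 = 0.55 | 25/26 = 96% |
| Logit, variance 0.5 | 70 × 0.463² = 15.0 | 70 × 0.0915² = 0.59 | 96% |

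Dropout at six months raises the discharge share to 97–99%.

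| Reading | Both gaps | Discharge gap only | Six-month gap only |
|---|---|---|---|
| Raw SD 0.08, 2 df | 93.2% | 92.2% | 9.3% |
| Logit, 2 df | 95.2% | 94.4% | 9.7% |
| Logit, 3 df | 92.7% | 91.7% | 8.7% |
| Beta simulation, precision 13, 2 df | 93.5% | not run | 9.8% |

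Over the six-month numbers tried, the last column runs from about 6% to 10%. A single six-month test of 13% v 12% has about 6–13% power. For 93% power on that 1-point gap alone, the raw SD of 0.08 would need 2 × 0.0064 × (1.960 + 1.476)²/0.01² ≈ 1,511 per arm before dropout. Across the settings used the range is about 1,410–1,520.

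**Step 3. What if a difference in change was meant?** Table 1 implies −2 points in the intervention arm (15 to 13) and +2 in control (10 to 12), a 4-point difference favouring the intervention (0.371 on the logit scale). With SE = √(4σ²(1−r)/70), no dropout, and power = Φ(difference/SE − 1.96):

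| r | Raw, SD 0.09 | Logit, variance 0.5 |
|---|---|---|
| 0 | 0.04/0.0215 = 1.86: 46% | 0.371/0.169 = 2.20: 59% |
| 0.5 | 0.04/0.0152 = 2.63: 75% | 0.371/0.120 = 3.11: 87% |
| 0.7 | 0.04/0.0118 = 3.39: 92% | 0.371/0.0926 = 4.01: 98% |

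The article states no correlation, so this reading can fall well short of 93% or reach it.

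**The case against.** The strongest reply is that the article does not say which likelihood ratio test was used. Section 2.6.1 does fit a group-by-time interaction. If that was the tested term, discharge serves as the reference before implementation, the change favours the intervention, and a correlation near 0.7 gives about the stated power. This stands. A reader might infer that almost all of the 93% certainly comes from the discharge gap. The documents support that only if a joint test was simulated. The reference in section 2.4 to multiple time points and the global test in section 2.6.1 suggest that it was, but do not prove it.

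Three further points stand in part.

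- **Direction.** A reader might infer that the reversed direction inflates the power. It does not: the test is two-sided, so swapping the row labels leaves the figure unchanged. Whether the labels were swapped or the cited data look like this cannot be told from the article. But swapped labels would still assume a 5-point benefit at discharge that shrinks to 1 point by six months.
- **Effect by discharge.** A reader might infer that no effect is possible by discharge. Section 2.2.3 refers to implementations of the medication review made during hospitalization, which does not sit easily with section 2.2.4. Some in-hospital effect is therefore not excluded, and the two sections must be reconciled.
- **Choice of analysis.** One might conclude that the global test should give way to a six-month test alone. That is a design choice, and the correction does not require it.

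**Conclusion.** The point holds in conditional form. Without any calculation, Table 1 contradicts the trial's aim in direction, and its largest gap falls where section 2.2.4 gives little ground for one.

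Under a joint test, which is the more natural reading, the 93% is nearly all power for the discharge gap. Without it, about 6–10% remains at 70 per arm. Under a difference-in-change reading, power runs from about 46% to 98% as r goes from 0 to 0.7, so 93% is possible but unsupported by anything stated.

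The joint-test figures assume independent time points and a common variance tuned to give roughly 93%. The change figures assume no dropout and the two spreads shown. Because the variance scale, degrees of freedom, correlation and age distribution are not stated, the percentages are ranges and not a recalculation of the authors' simulation. On either reading, the article does not show that 93% is the power to detect fewer PIMs after discharge.

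**What to change.** 1. Correct the direction or the row labels of Table 1.
2. Set the arms equal at baseline and at any point before the intervention can act, after reconciling sections 2.2.3 and 2.2.4 on what may change by discharge.
3. State the assumed post-discharge difference in favour of the intervention, the within-patient correlation and the scale of the variance.
4. Name the contrast the power refers to (joint test, difference in change, or a single time point) and its degrees of freedom.
5. Rerun the simulation with the planned analysis at 70 per arm, and replace the 93% with the result.

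The cost is a rerun of the existing do-file with revised inputs and a correction to section 2.4. N and the planned primary analysis can stay. The likely downside is a less favourable stated power, which is better known before the results are read.

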### 2.5. Randomization

One hundred and forty patients (70 in each group) will be included and randomized. A simple block randomization method will be used [69], with patients randomized by a computer-generated randomization sequence program using REDCap [70,71]. Variable blocks are used to adjust for assignment bias. The Medication Coordinator will be blinded to the size of the blocks and will not be able to predict patient group allocation.

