## 2. Methods and analysis

### 2.1. Study design

The study is a single-center randomized controlled trial assessing a complex intervention with the Medication Coordinator. The screening, enrolment, randomization to the interventions, and assessments will be conducted by MS only (Fig 1). The reporting of this protocol follows the guideline for Standard Protocol Items: Recommendation for Interventional Trials–SPIRIT 2013 [44] (S1 File). The randomized clinical trial reporting will follow the CONSORT guidelines [45].

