#### 2.1.1. Recruitment of patients

Patients will be recruited from the Endocrinology and Nephrology Unit at the Hospital Sønderjylland. The ward treats renal disease, diabetes, hormone disorders, patients with diabetic ulcers, and internal medicine patients. The ward comprises 16 beds distributed by rooms for two or four patients. Recruitment will commence in *medio* May 2024 and be completed by *ultimo* May 2025. We expect to include four patients weekly.

The inclusion criteria comprise all hospitalized patients 18 years or above, and are prescribed at least five medications specified in the Electronic Patient Journal (EPJ).

Patients are not eligible for inclusion if they are unable to communicate in Danish, are cognitively impaired, e.g. suffering from dementia or Alzheimer’s, or cannot cooperate due to, e.g. hallucination or aggressive behavior.

The Medication Coordinator will screen patients for eligibility and include relevant patients in the study. After the initial screening, the ward nurses are consulted regarding patient capability to contribute to a conversation about medication based on the patients habitual condition. The Medication Coordinator performs this task so the everyday workload of the ward staff is not increased or disturbed.

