The effect of a medication review not only depends on the different components of the intervention itself but is also highly dependent on the patient’s subjective experience [5,47]. Thus, the complex intervention model may have several positive effects, which we will assess using secondary outcomes like patient-reported quality of life and treatment burden. Some patients might find the medication review with the Medication Coordinator effective, but for others, the information passed onto the GP in the discharge summary may be more effective. Nevertheless, all components are a part of the complex intervention.

Because the resources in the healthcare sector are scarce, prioritizing the patients most in need of a medication review is a priority [84]. A Danish study in general practices has demonstrated that patients with a MERIS score above 13 would most likely benefit from a medication review [37]. The MERIS screening tool is based on patients’ renal function, the total number of medications, and the risk of harm or interactions caused by drugs [31,37]. These factors might be just as high a risk for experiencing an adverse drug-event as age. Age has been associated with increased risk of experiencing an adverse drug-event due to changes in pharmacokinetic and pharmacodynamic [85]. This may be explained by many drugs being renal excreted, hence may need dose-adjustments. These factors might indicate a risk for experiencing an adverse drug-event similar to age, which has been associated with increased risk of experiencing an adverse drug-event. This may be explained by many drugs being excreted renally, hence may need dose-adjustments. Therefore, there is a need to adjust the dose according to renal function. Patients of all ages are included in this study as younger patients could also have a high MERIS score and benefit from the intervention.

Another strength of this study is the intention to secure the information flow in the transition from the hospital to the patient’s home. Medication changes and follow-up appointments with healthcare professionals are presented to the patient by *My Medication Plan* and to the GPs via the electronic discharge summary.

A strength of the data generation process is that one person collects it. It can also be a limitation of the study as there is a risk of the Pygmalion Effect [86]. It is a limitation that the first author is performing the complex intervention.

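### Hiding variable block sizes does not stop better-than-chance prediction of allocation by the one unblinded person who enrols, randomises and treats every patient

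*Protocol article*

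**What the plan says.** Section 2.1 describes a single-centre trial and gives four tasks to one individual: "The screening, enrolment, randomization to the interventions, and assessments will be conducted by" one person only. Section 2.1.1 gives screening and inclusion to the Medication Coordinator: "The Medication Coordinator will screen patients for eligibility and include relevant patients in the study". The Coordinator also carries out the medication reviews and the follow-up call (sections 2.2.1, 2.2.3 and 2.2.4).

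Eligibility includes items that need judgement. Patients are excluded if they "cannot cooperate due to, e.g. hallucination or aggressive behavior", and after initial screening "the ward nurses are consulted regarding patient capability to contribute to a conversation about medication".

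Section 2.5 specifies variable blocks, a computer-generated sequence in REDCap and 70 patients per group, and names no stratification. It concludes that "The Medication Coordinator will be blinded to the size of the blocks and will not be able to predict patient group allocation". Section 2.6 blinds the data analyst. No text blinds the Coordinator to allocations already made.

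**The concern.** The sentence in section 2.5 treats ignorance of block size as enough to prevent prediction. In permuted blocks the arms return to equality at the end of every block. Someone who knows the past allocations can therefore guess that the next patient goes to the arm that is behind, whatever the block sizes are.

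That the Coordinator knows every past allocation is an inference, but a firm one: the same person randomises all patients and treats one of the arms. With one site, no stratification and about four inclusions a week, a tally is easy to keep, even without intending to.

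A guess matters only if it can influence who is enrolled. Whether a patient can cooperate, or is capable of a conversation about medication, is settled before randomisation and has no stated scale or cut-off. If those judgements leaned one way when the intervention arm was expected, the arms could differ at entry in engagement or capability. That could affect the comparison of potentially inappropriate medications (PIMs) and the patient-reported outcomes. The Discussion says contamination would pull the estimate towards no difference. Selection at enrolment could act in either direction.

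**Working it through.** The article gives no figure for predictability, so there is none to reproduce.

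**Inputs.** 140 patients, 1:1, in variable blocks (section 2.5); one site and one enrolling person (sections 2.1 and 2.1.1); stated power 93% (section 2.4). Block sizes are not given. The sets below are assumptions, with each size in a set equally likely.

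**Guessing rule.** Guess the arm with fewer patients so far; toss a coin when the arms are level. No block size is used.

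**Step 1: expected correct guesses in one block of size 2m** = m + (2^(2m)/C(2m,m) − 1)/2.

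- Size 2: 1 + (4/2 − 1)/2 = 1.500, or 75.0%
- Size 4: 2 + (16/6 − 1)/2 = 2.833, or 70.8%
- Size 6: 3 + (64/20 − 1)/2 = 4.100, or 68.3%
- Size 8: 4 + (256/70 − 1)/2 = 5.329, or 66.6%
- Size 10: 5 + (1024/252 − 1)/2 = 6.532, or 65.3%

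These are for fixed sizes. The protocol varies them, so the next step is the relevant one.

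**Step 2: variable blocks.** In a long sequence the share correct is the sum of the expected correct guesses divided by the sum of the sizes. For {2,4} this is (1.500 + 2.833)/6 = 72.2%. For {6,8,10} it is (4.100 + 5.329 + 6.532)/24 = 66.5%. Simulating 140 allocations (10,000 runs per set) gives:

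| Assumed sizes | Share guessed correctly | Correct of 140 |
|---|---|---|
| {2,4} | 72.2% | 101.1 |
| {2,4,6} | 70.2% | 98.3 |
| {4,6} | 69.2% | 96.9 |
| {4,6,8} | 68.0% | 95.2 |
| {4,8} | 67.9% | 95.1 |
| {6,8,10} | 66.3% | 92.8 |
| Unrestricted | 50.0% | 70.0 |

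Across the variable sets the arms are unequal before 55.5% to 66.9% of allocations. At those points the guess is right 74.5% to 90.0% of the time.

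**Step 3: what hiding the sizes achieves.** An observer who also knew the largest block size would be certain of the next allocation for about 5.5% of patients with {2,4}, 1.0% with {4,6}, 0.8% with {2,4,6} and 0.2% with {4,6,8}. The Coordinator is not told the sizes.

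**Step 4: price of unrestricted 1:1 allocation.**

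- Expected absolute difference between arms: √(2 × 140/π) = 9.4 patients.
- 95% range for one arm: 70 ± 1.96 × √140/2 = 70 ± 11.6, so about 58:82 to 82:58.
- Relative efficiency at 58:82: 4 × 58 × 82/140² = 0.971.
- Power of 93% corresponds to 1.960 + 1.476 = 3.436. Then 3.436 × √0.971 − 1.960 = 1.425, which gives 92.3%.

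**The case against.** The strongest defence is that section 2.5 uses ordinary concealment language for a recognised method, and that to predict means to know the next assignment. On that reading the safeguard largely works: step 3 shows that certainty is rare, and REDCap would normally withhold the assignment until the patient is entered. This stands, and the design deserves the credit. It does not rescue the sentence, which excludes prediction altogether.

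Much of the eligibility rule also leaves limited room for discretion: age, at least five medications in the patient record, ability to communicate in Danish, and cognitive impairment with examples. The nurses contribute to the capability judgement, which refers to the patient's habitual condition. That narrows the opening without closing it, since the Coordinator makes the inclusion.

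A reader might infer that the trial will be biased, or that any imbalance would be invisible. The article supports neither. Nothing shows that guesses would be acted on, and a guess rate is not a bias. PIMs, the EQ-5D, the treatment burden questionnaire (MTBQ) and the medication risk score (MERIS) are all measured at inclusion and would show part of any difference between arms. Engagement and capability are not measured and would not show.

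Finally, the Discussion concedes that "It is a limitation that the first author is performing the complex intervention", and names the Pygmalion effect, contamination, transfer bias and social-desirability bias. None of these is selection at enrolment.

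**Conclusion.** The statement that the Coordinator will be unable to predict allocation describes a property this design does not have. What remains is probabilistic guessing, right about 66% to 72% of the time against 50% by chance, not open access to the list. The exact rate depends on the assumed block sizes, but it was above 66% in every variable set tried. The conclusion also assumes that the one person keeps track of past allocations, which the stated roles make hard to avoid.

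Selection at enrolment is therefore possible through the judgement-based part of eligibility. Whether it would occur, and how large it would be, cannot be derived from the article. The sentence needs correcting and the risk needs either removing or disclosing.

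**What to change.** **Preferred change.** Replace the permuted blocks in the REDCap allocation table with unrestricted 1:1 randomisation of the 140 patients, so that past allocations carry no information. Reword 70 per group as the expected number in the Abstract and sections 2.4 and 2.5. No extra staff are needed. The cost is unequal arms: about 9 patients apart on average, with a 95% range out to 58:82. Even there, power falls from 93% to about 92.3%. That figure takes the stated 93% at face value and uses a normal approximation, not the article's beta-regression simulation with dropout.

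**If variable blocks are kept**, or recruitment is too advanced to change the scheme, replace the claim in section 2.5 with a statement that certain prediction is unlikely but better-than-chance prediction remains possible. Add selection at enrolment to the limitations in section 3. This costs two sentences.

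Locking the eligibility decision and baseline data before the allocation is shown is good practice, but it does not cure this problem: the guess comes before the eligibility decision and may already have shaped it.
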